### Statistical methods

Follow-up time will be calculated for each participant from date of randomisation until the first among: date of outcome, date of death, or 22 October 2002 (when the trial was formally halted). The intention to treat principle will be adopted when assessing treatment effects, participants being classified according to randomisation group and analyses being made comparing HRT (combined HRT plus estrogen only HRT) or combined HRT alone with placebo, and combined HRT with estrogen only HRT. To account for the prospective nature of the data, Kaplan-Meier outcome-free survival curves will be computed and Cox proportional hazard models fitted (after graphically checking the underlying proportional hazards assumptions). The results will be reported as estimated hazard ratios for the effect of HRT versus placebo, combined HRT versus placebo or combined HRT versus ERT, (with 95% confidence intervals), with associated likelihood ratio tests for their significance [62].

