### Follow-up

It was planned to recruit women over a three year period and to end the trial nine years after the last participant was randomised giving a median of 10.5 years follow up, and a maximum of 12 years. Women were to be seen at their general practice at 4, 14, 27, 40 and 52 weeks and then 6 monthly. Nurses contacted participants between visits, by telephone, to provide advice and support as required. A final visit was to take place as soon as possible after the closure of the trial.

Because of the decision in October 2002 to close the trial early when the WHI results indicated that the likely balance of risks and benefits of HRTwas unfavourable the median follow up time for WISDOM was 11.9 months (IQR: 7.1 months to 19.6 months).

Patient compliance was assessed at each visit by tablet count. At the annual visit information was collected on risk factors, possible adverse events, all outcomes and on other medical history to check that patients remained eligible (see Additional file 1). At other visits information was collected on risk factors, possible adverse events, primary and secondary outcomes and on other medical history to check that patients remained eligible (see Additional file 1). There was provision for recording information received by the nurse or the GP from the patient, and with the patient's permission, from a friend or a relative between follow-up visits. A further check of general practice medical records was made annually.

Outcomes were assessed at face to face interviews between the patient and the nurse, using validated questionnaires wherever possible, and entering data directly onto laptop computers using a suite of software specially designed for the trial which included a real time patient management system in accordance with the protocol. Electronic data checking at the time of collection incorporated extensive checks for plausibility, consistency and completeness. Data were sent to the co-ordinating centre within one week of collection by modem link within the UK and via a standard File Transfer Program server site from Australia and New Zealand. A member of the study team, who was blinded to treatment allocation, obtained any data needed to confirm a clinical event from the GP, hospital or coroner.

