It had been planned to ascertain fatal end-points and cancer registrations in the UK via the National Health Service Central Register, in Australia via the National Death Index database and in New Zealand via National Health Index number tracing, death registrations, hospital records and the New Zealand Cancer register but with the early closure this was not pursued.

To fully assess the long-term effects of HRT and to investigate changes following discontinuation of treatment, follow up by medical records in the general practice and national records had been planned for a further five years after treatment but following closure these plans were abandoned.

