### Discontinuation of trial treatment

Permanent discontinuation of trial treatment was required if any of the exclusion criteria for the trial were confirmed during follow up. If participants developed symptomatic or active gall bladder disease a temporary interruption of treatment was made and if the participant subsequently had a cholecystectomy they were invited to recommence trial treatment. A temporary interruption of treatment was required to investigate sudden loss of vision, onset of proptosis or diplopia.

When trial outcomes occurred that were not trial exclusions (myocardial infarction, unstable hospitalised angina pectoris, cerebrovascular accident, subarachnoid haemorrhage, TIA, osteoporotic fractures) participants were able to remain on their allocated treatment to contribute to other outcomes. However, a temporary interruption of treatment could be initiated at the discretion of the GP or other clinician or by the participant. To reduce the risk of venous thromboembolism, a temporary interruption could be made during hospitalisation and following accidents resulting in immobilisation. Trial treatment could also be discontinued at the discretion of the GP for symptoms possibly associated with trial treatment, other medical or non-medical reasons. Participants were free to initiate withdrawal from the trial or temporary interruption of treatment without giving a reason.

GPs and participants were encouraged to try a temporary interruption of treatment first and were requested to discontinue treatment permanently only after consultation with the trial clinician and after all efforts had been made to keep the patient on randomised treatment.

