### Minimising loss to follow up

All patients who discontinued trial treatment were followed up and every effort was made to contact patients after non-attendance at follow up appointments to minimise losses to follow up. Where participants did not attend for visits, but had given permission for their medical records to be accessed, annual and final searches were undertaken.

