## Results

The trial was prematurely closed during recruitment following publication of early results from the Women's Health Initiative. At the time of closure, 56583 had been screened, 8980 entered run-in, and 5694 (26% of target of 22300) randomised. Those women randomised had received a mean of one year of therapy, mean age was 62.8 years and total follow-up time was 6491 person years. The results will be published separately.

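### The follow-up rule has no end date for women lost to follow-up, so any whose outcome status was not known to 22 October 2002 are credited with unobserved event-free time

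*Protocol article*

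**What the plan says.** Under Statistical methods, follow-up for every participant runs "until the first among: date of outcome, date of death, or 22 October 2002 (when the trial was formally halted". That list is complete as written, and neither loss nor last contact is on it. The times feed survival methods: "Kaplan-Meier outcome-free survival curves will be computed and Cox proportional hazard models fitted". The analysis is by intention to treat.

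Three other places show that status could become unknown before closure:

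- **Discontinuation of trial treatment:** "Participants were free to initiate withdrawal from the trial or temporary interruption of treatment without giving a reason". Leaving the trial is named separately from interrupting treatment.
- **Minimising loss to follow up:** for women who did not attend "but had given permission for their medical records to be accessed, annual and final searches were undertaken", so the searches depended on permission.
- **Follow-up:** tracing of deaths and cancer registrations through national registers had been planned, "but with the early closure this was not pursued".

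Other statements narrow the gap. Women who stopped trial treatment stayed in follow-up (Minimising loss to follow up). General practice records were checked every year, and a final visit was planned (Follow-up). Consent to record use was sought from all women (Screening). Closure visits were funded (Background). The article does not give the uptake of that consent, the number lost, or any statement that records were searched to 22 October 2002 for everyone.

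**The concern.** Kaplan-Meier and Cox methods treat all credited time as time in which an event would have been seen. A fixed calendar end date meets that condition only for women whose status is known to that date. For the rest, the rule adds time to the denominator while events in that time cannot enter the numerator.

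Two consequences need to be kept apart. Any uncovered loss, balanced or not, lowers the estimated event rates and raises the outcome-free curves. That matters because the stated aim is the balance of long-term benefits and risks, which is read from absolute rates. The hazard ratio is affected only when the uncovered share of time differs between arms.

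**Working it through.** **Inputs from the article**

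- Randomised: "5694 (26% of target of 22300) randomised".
- Person-time: "total follow-up time was 6491 person years".
- Follow-up distribution: "the median follow up time for WISDOM was 11.9 months (IQR: 7.1 months to 19.6 months".
- Placebo cardiovascular risk: 39 per 1000 over ten years (Sample size and comparisons).

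**1. The plan's own figure.** Mean follow-up = 6491 / 5694 = 1.14 years, or 13.7 months. This is compatible with the stated median and quartiles. It does not show how lost women were counted, and the total cannot be rebuilt without individual dates.

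**2. Effect on rates.** The events seen are the same under either version, so the rate under the written rule divided by the rate with censoring at loss equals observed time / credited time. If uncovered loss occurs at a constant hazard h = -ln(1 - annual loss), a woman with potential follow-up T contributes observed time (1 - exp(-hT)) / h. Hence

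observed fraction = mean[(1 - exp(-hT)) / h] / mean[T].

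For T, a Weibull distribution was fitted to the stated quartiles (shape 1.50, scale 15.7 months, capped at 3.5 years). Its quartiles are 6.8, 12.3 and 19.5 months. All loss rates are **assumed**.

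| Uncovered loss per year, both arms | Observed fraction | Rate understated by |
|---|---|---|
| 2% | 0.983 | about 2% |
| 5% | 0.958 | about 4% |
| 10% | 0.917 | about 8% |

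A simpler check gives every woman the mean of 1.14 years. At 5% a year, h = 0.0513 and hT = 0.0585, so the fraction is (1 - exp(-0.0585)) / 0.0585 = 0.971, a shortfall of 3%. The spread of follow-up times adds the rest, because longer follow-up leaves more time to lose.

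**3. Effect on the hazard ratio.** Multiplier = observed fraction (HRT) / observed fraction (placebo).

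| Assumed uncovered loss per year, HRT v placebo | Multiplier |
|---|---|
| equal (2%, 5% or 10% in both) | 1.00 |
| 5% v 2% | 0.958 / 0.983 = 0.975 |
| 10% v 5% | 0.917 / 0.958 = 0.957 |
| 5% v 10% | 0.958 / 0.917 = 1.045 |
| 15% v 5% | 0.877 / 0.958 = 0.915 |
| 20% v 5% | 0.837 / 0.958 = 0.874 |

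Cox models fitted to large simulated data sets agree. Written rule v censoring at loss gave 0.681 v 0.682 (5%/5%), 0.730 v 0.730 (10%/10%), 0.654 v 0.681 (10%/5%) and 0.612 v 0.696 (20%/5%). Equal loss leaves the ratio alone; unequal loss moves it by about the amounts in the table.

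**4. Set against random error.** If the design rate were constant, 0.0039 x 6491 gives about 25 cardiovascular events. With two equal arms the standard error of the log hazard ratio is about 2 / sqrt(25) = 0.4, and exp(1.96 x 0.4) = 2.2. The 95% limits would then lie a factor of about 2.2 either side of the estimate.

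**The case against.** The strongest reply is that observation was better than the rule suggests. Stopping tablets did not end follow-up, general practice records were checked annually, non-attenders who had given permission had annual and final searches, and closure visits were funded. For all these women 22 October 2002 is ordinary administrative censoring. This stands, and it confines the point to women who left and were not covered by a later contact or search. It does not remove the point: permission was needed, register tracing was dropped, and with a median follow-up of 11.9 months about half the women may not have reached an annual record check.

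A reader might also infer that the rule biases the hazard ratios, and specifically hides harm on combined HRT because bleeding drove women out. The article does not support that. Equal loss leaves the ratio unchanged. The bleeding passage (Vaginal bleeding in women with a uterus) describes women withdrawing from randomised treatment, not from follow-up, under a procedure revised in January 2001. Counting back the upper quartile of 19.6 months from closure gives about March 2001, so roughly three quarters of the women were randomised after the revision. Heavier loss on placebo would push the ratio the other way.

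Next, shifts of 3% to 13% are small beside a factor of 2.2. That is fair for this trial read alone. But the article expects its breast cancer data to be used in a meta-analysis, where pooling reduces random error and leaves systematic error in place.

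Finally, handling of losses is often left to a fuller document. Here, however, the article states a rule for each participant, and applied as written that rule gives the wrong person-time.

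**Conclusion.** The point holds in a limited form. As written, the rule credits unobserved event-free time to any woman whose status was not known to closure. Rates are then understated by about 2%, 4% and 8% at uncovered losses of 2%, 5% and 10% a year. The hazard ratio can move either way, but only if uncovered loss differs by arm: x0.874 to x1.045 across the unequal scenarios tried. These sizes rest on assumed loss rates, a constant loss hazard, no record coverage for those lost, and a fitted follow-up distribution.

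The article gives no count of losses, so it shows neither that the hazard ratios are biased nor that 6491 person-years is inflated. The correction is worth making before analysis, but its importance is moderate and it does not by itself put the trial's comparisons in doubt.

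**What to change.** Amend Statistical methods as follows:

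- Women who were seen, or whose records were searched, up to 22 October 2002 are followed to that date, unless an outcome or death comes first.
- All other women are censored at the last date on which outcome status is known (visit, contact or completed record search), unless an outcome or death comes first.
- The number censored before 22 October 2002 is reported by arm, so that readers can judge whether loss was balanced.
- The fixed-date version is kept as a sensitivity analysis.

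If records were in fact searched to 22 October 2002 for every woman, saying so would settle the matter with no change of method.

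The cost is one derived date per woman and slightly fewer person-years. Censoring at last known status still assumes that loss is unrelated to risk, which is a further reason to report losses by arm.

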## Methods

### Trial design

WISDOM was designed as a double blind randomised placebo controlled trial. The design allowed for two comparisons: the main comparison between HRT, mainly combined HRT, and placebo; and in hysterectomised women only, between estrogen alone and combined HRT. The different stages of the trial from identification of potential participants through to the closure visit are summarised in Figure 1 and the data collected at the different stages is outlined in Additional file 1.

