### Randomisation

After the second run-in visit women who were eligible and willing to participate were randomised centrally and appropriate medication dispatched to the practice in time for the baseline randomisation visit. Participants were assigned to treatment in accordance with the schema at Figure 3 using a computer based, stratified block randomisation program to ensure that within each stratum the treatment groups were of virtually equal size. The stratification was based on hysterectomy status and HRT use at the time of randomisation. In stratum one, women with a uterus were randomised to combined HRT therapy using a block size of 16. In stratum two, hysterectomised women who were only prepared to take active treatment were randomised to estrogen only HRT or combined HRT using a block size of 16. In stratum three, hysterectomised women were randomised to estrogen only HRT, combined HRT or placebo using a block size of 24.

The baseline questionnaire at the randomisation visit (see Additional file 1) covered risk factors, possible adverse events, all outcomes, quality of life and other medical history to check that they remained eligible. Use of health services and details of the severity of certain conditions eg, systemic lupus erythematosus were obtained from the patients' notes. The nurse measured height, weight, and waist and hip circumference using standard operating procedures and the GP then made a final decision on eligibility. A patient was recorded as entering randomised treatment if she left the surgery with her first pack of randomised treatment tablets.

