• In the absence of reliable estimates of the incidence of unstable angina for women in the relevant age group, the best estimate was a rate of about 1 per 1000 women per year. Over the ten years of the trial this rate would generate 9.7 unstable angina events per 1000 women entered. However, it was estimated that 50% of these would lead to myocardial infarction, giving an incidence of independent unstable angina events of 4.8 per 1000 women.

• A healthy volunteer effect leading to event rates only 67% of those based on the sum of fatal and non-fatal episodes in the general population.

• Based on feasibility studies and current use of and interest in HRT 20% of the trial population being in the age range 65–69 years and 80% being distributed equally across the three five year age bands, 50–54, 55–59, 60–64 years.

• A 3 year recruitment, which would give 33% of women in study for 11 years, 33% in study for 10 years and 33% of women in study for 9 years.

Using these assumptions the average probability of a major cardiovascular event within ten years in women in the age group 50–69 was estimated to be 0.039.

For the main comparison of HRT versus no HRT, only women who could be randomised to receive placebo could contribute (strata 1 and 3, Figure 3). Based on feasibility studies the proportions expected in the different strata were: stratum 1, 58% equally divided between combined HRT and placebo; stratum 2, 22% equally divided between combined HRT and estrogen-only HRT; stratum 3, 20% equally divided between combined HRT, estrogen-only HRT and placebo. The majority of women on HRT (~84%) would be on combined HRT. Of the total sample size, 78% would be used to compare HRT with placebo (the remaining 22% contributing to the ERT v PERT comparison). The sample sizes have been calculated to achieve significance in a combined HRT versus no HRT comparison, with equal numbers of women randomised to combined HRT and placebo. The target sample size of 22300 gives statistical power of 80% (at 5% level of significance) to detect a reduction of 29% in the cardiovascular end-point. Power for an HRT (combined HRT plus estrogen only HRT) versus no HRT comparison would be slightly increased by the inclusion of hysterectomised patients (within stratum 3) randomised to estrogen-only HRT.

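### The pooled HRT versus placebo analysis should state that it is stratified by randomisation stratum, because active:placebo allocation is 1:1 in stratum 1 and 2:1 in stratum 3

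*Protocol article*

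**What the plan says.** All references are to the protocol article.

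- **Randomisation:** "The stratification was based on hysterectomy status and HRT use at the time of randomisation". Treatment is allocated in blocks within each stratum.
- **Sample size and comparisons**, expected split for women with a uterus: "stratum 1, 58% equally divided between combined HRT and placebo". Stratum 2, which has no placebo arm, is expected to supply 22% of the sample, half on each HRT regimen. For hysterectomised women not taking HRT, the section gives: "stratum 3, 20% equally divided between combined HRT, estrogen-only HRT and placebo".
- **Same section**, on HRT versus no HRT: "only women who could be randomised to receive placebo could contribute (strata 1 and 3, Figure 3". It limits the estrogen-only versus combined comparison to stratum 2 and the actively treated women of stratum 3.
- **Same section**, basis of the sample size: "The sample sizes have been calculated to achieve significance in a combined HRT versus no HRT comparison, with equal numbers of women" in each arm. It mentions adding the estrogen-only women of stratum 3 to the HRT side only as a small gain in power.
- **Trial design:** "the main comparison between HRT, mainly combined HRT, and placebo".
- **Statistical methods:** "analyses being made comparing HRT (combined HRT plus estrogen only HRT) or combined HRT alone with placebo", plus combined versus estrogen-only HRT, by Kaplan-Meier curves, Cox models and likelihood ratio tests, with women classified by randomised group. It does not mention stratum, either as a stratifying variable or as a covariate, and does not repeat which strata enter which comparison.

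**The concern.** Stratified randomisation makes the arms comparable within each stratum. Comparability carries over to a simple pooled comparison only when the allocation ratio is the same in every stratum. For pooled HRT versus placebo it is not, so the pooled HRT group holds proportionately more stratum 3 women than the placebo group does.

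If stratum 3 women (hysterectomised, not on HRT) have a different underlying rate of coronary disease, fracture or breast cancer from stratum 1 women, a comparison that ignores stratum mixes that difference into the treatment effect. The resulting bias does not diminish with more events. The article gives some reason not to assume equal risk: its account of evidence since closure notes that women in the US trial, particularly in the estrogen-only arm, which enrolled hysterectomised women, were more overweight than average. It gives no event-rate ratio between hysterectomised and other women.

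What is at stake is one named hazard ratio, and the pooled Kaplan-Meier curves that go with it.

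**Working it through.** **1. The plan's own allocation figures** (inputs from Sample size and comparisons)

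- Combined HRT in strata 1 and 3: 58%/2 + 20%/3 = 29% + 6.67% = 35.67% of the sample.
- Estrogen-only in stratum 3: 20%/3 = 6.67%.
- Placebo: 29% + 6.67% = 35.67%.
- Share of HRT women on combined HRT: 35.67/(35.67 + 6.67) = 84.3% (article: about 84%).
- Strata 1 and 3 together: 58% + 20% = 78% (article: 78%).
- Combined versus estrogen-only: 22300 × (0.22 + 2 × 0.20/3) = 7879 (article: about 8,000).
- Power for combined HRT versus placebo, 22300 × 0.3567 = 7954 per arm, 0.039 versus 0.031, two-sided 5%: 78.4% (article: 80%; at 23000 it is 79.6%).

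The stated figures reproduce closely, so the stratum shares can be relied on.

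**2. Stratum 3 share of each arm**

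- Pooled HRT: 13.33/42.33 = 31.5%.
- Placebo: 6.67/35.67 = 18.7%.
- Combined HRT alone: 6.67/35.67 = 18.7%, the same as placebo.
- Combined versus estrogen-only: 1:1 in stratum 2 and 1:1 in stratum 3, so the two arms have the same stratum mix.

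Only the pooled contrast is unbalanced.

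**3. Effect on a crude pooled hazard ratio**

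Let R be the event-rate ratio, stratum 3 to stratum 1, without treatment. R is not in the article and is assumed. With rare events the crude hazard ratio is close to the ratio of the mixed rates, so it is multiplied by

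(1 + 0.315(R − 1)) / (1 + 0.187(R − 1)).

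The last column applies this to the diluted cardiovascular effect, 1 − 0.29 × 0.7 = 0.797. This uses the article's approximation that 70% of the HRT group are treated for the full ten years.

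| R (assumed) | Factor | A true 0.797 would read as |
|---|---|---|
| 0.7 | 0.959 | 0.765 |
| 0.8 | 0.973 | 0.776 |
| 1.0 | 1.000 | 0.797 |
| 1.2 | 1.025 | 0.817 |
| 1.3 | 1.036 | 0.826 |
| 1.5 | 1.059 | 0.844 |
| 2.0 | 1.108 | 0.883 |

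In a model stratified by randomisation stratum the factor is 1.00 for every R.

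**4. Consequence at the planned size** (22300 women, placebo probability 0.039)

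If stratum were ignored, the two-sided error rate would be about 6.2% at R = 1.2 and 11.9% at R = 1.5, instead of 5%. Power against 0.797 would be about 72% and 58%, instead of 81%.

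**5. Consequence in the halted trial**

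Statistical methods censors at 22 October 2002, and the article reports 6491 person-years. Assume a flat hazard of 0.039 per ten years and the planned 78% of person-years in strata 1 and 3.

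- Events: 6491 × 0.78 × 0.0039 ≈ 20.
- HRT share: 42.33/78 = 54.3%, so about 10.9 and 9.1 events.
- SE of the log hazard ratio: √(1/10.9 + 1/9.1) ≈ 0.45.
- Bias at R = 1.5: ln(1.059) = 0.057, or 0.057/0.45 ≈ 0.13 SE. The two-sided error rate is about 5.2%. With twice as many events it is about 5.4%.

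**The case against.** The strongest case against has four parts.

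- **Silence is not a statement.** A reader might infer that the Cox model is unstratified. The section never says so. It is one paragraph of a condensed article, and strata and covariates are commonly left to a fuller plan that is not shown. This stands: what can be said is only that the text as written leaves the pooled contrast open to confounding.
- **The strata are already restricted.** A reader might fear that stratum 2, which has no placebo arm, would be added to the HRT side. The sample size section rules that out and also limits the combined versus estrogen-only comparison. This stands, so only the stratification itself would be new.
- **The sized comparison is unaffected.** A reader might infer that the trial's main comparison is confounded. Trial design does describe the main comparison as HRT, mostly combined, against placebo, but the sample size rests on combined HRT alone, which is balanced and is also to be reported. This stands. The wording that joins the pooled and combined-only contrasts is a secondary matter: the end of Statistical methods lists a hazard ratio for each, and the natural reading is that all are reported.
- **The bias is small and hypothetical.** It needs an assumed risk ratio, and random error dominates in the halted trial. This stands on size, but it is no reason to leave an avoidable bias in a named estimate.

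The imbalance is also strictly one of stratum: stratum 1 includes women with sub-total hysterectomy, so 31.5% and 18.7% are not exact proportions by hysterectomy status.

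**Conclusion.** The point holds for one contrast. The allocation ratios differ between strata 1 and 3 once the HRT arms are pooled, and the analysis text names that pooled comparison without mentioning stratum. Read literally, it could yield a hazard ratio off by about −4% to +6% for assumed rate ratios of 0.7 to 1.5, with no bias if baseline risk is the same in both strata. This rests on the planned stratum split, a rare-event approximation and an assumed risk ratio; the article gives neither the achieved split nor the risk ratio.

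The larger error rates and power losses belong to the planned 22300 women, not to the data that the section now governs. The article does not support a claim that the model is unstratified or that the trial's conclusions are confounded. This is a free improvement, not something that must be corrected before the analysis can proceed.

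**What to change.** Add to Statistical methods wording such as: *Cox models and likelihood ratio tests will be stratified by randomisation stratum. Comparisons with placebo will use strata 1 and 3; combined versus estrogen-only HRT will use strata 2 and 3. Kaplan-Meier curves for pooled HRT versus placebo will be shown by stratum or standardised to a common stratum distribution.*

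The restrictions repeat what the sample size section already implies; the stratification is the new element. It would also help to say there that combined HRT versus placebo is the contrast on which the trial was sized.

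The cost is two or three sentences. Stratum was used to randomise every woman, so no further data are needed, and the article says that the results are still to be published.
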